### Sample size

Power calculation for ANCOVA analysis was conducted with G*Power 3.1.3. In order to detect a medium effect size of 0.4 (based on reviews and meta-analyses of psychosocial and cognitive behavioral interventions in cancer survivors) [25, 38–40] with an alpha of 0.05 and a power of .80, a sample size of 190 participants is calculated. To correct for the baseline assessment as covariate the sample size is multiplied with the factor (1- *r*^2^). The *r* gives the correlation between pre-intervention and post-intervention distress. Based on a meta-analysis of pre-intervention distress as a moderator in psychosocial interventions for distress in cancer patients, this is an average of 0.6 [41], resulting in a sample size of 128 patients. Taking into account a dropout rate of approximately 20% a sample of 160 patients (80 patients per condition) will be included at baseline.

### The CORRECT-intervention

#### Developmental process

Experienced clinical psychologists, cognitive behavioral therapists and researchers (JP, BT, EC, AB, LL) elaborated the website and treatment manual, including a detailed description and session checklist of each therapy session. The intervention was developed according to the theoretical framework of CBT [42] and a behavioral change model of internet interventions [43]. Further, we used the TIDieR checklist, a template for intervention description, in the developmental process [44].

The development of the CORRECT intervention consisted of different parallel stages. We started with a literature search and several expert meetings with therapists and researchers to define the core components of the intervention. In the same period, two brainstorming sessions including members of the researcher team and ICT specialists were organized to develop the structure of the website. The website was designed with technical guidance from Karify (https://www.karify.com/; Utrecht, the Netherlands), an e-health application for online information, communication and treatment in healthcare. At the start of developing the CORRECT intervention there were three existing websites which had been developed by the department of Medical Psychology in the Radboudumc [45–47]. First, was the web-based self-management intervention BREATH, designed to support the psychological adjustment of women after primary breast cancer treatment [45]. The website SWORD was developed as part of a blended therapy to manage high levels of FCR in breast, prostate and colorectal cancer survivors [46]. Following a study on psychological adjustment in the first year after diagnosis amongst Dutch CRCS (unpublished data) [48] the content of BREATH was adjusted and translated to a CRC specific self-management website. A multidisciplinary team including specialized CRC nurses, a general practitioner, psychologists, researchers and CRC patients participated in adapting this website. Finally, a think aloud study was held with five CRCS to optimize the website. This CRC specific self-management website was the basis for the CORRECT website that was further developed in accordance with the process and content of these three existing websites.

The content of the treatment manual and the website for the CORRECT-intervention was then revised by the members of the research team. The first complete version of the intervention was sent to a multidisciplinary reading committee, consisting of two nurse specialists, a surgeon, two healthcare psychologists and two CRCS. The members of the committee were asked to provide comments and suggestions in order to further improve the content of the intervention. In addition, they completed an evaluation questionnaire, which consisted of 13 items on a 5-point Likert Scale ranging from 0 to 5 (higher score indicating more positive impression) (e.g. “*What do you think of the coherence between the texts and the exercises?”*). The content of the intervention was rated with a mean score of 4.23. The content and format of the intervention were revised using feedback given by the reading committee.

In order to optimize the website, usability (i.e. the ease with which participants can use the website) of the self-management website was studied in a formal usability testing phase. Three CRCS were asked to use the website. A scenario-based think aloud procedure was employed [49]. In this procedure, the three participants were asked to verbalize their thoughts while completing tasks or going through scenarios that pose a problem. These ‘think aloud procedures’ were filmed. A researcher (LL) and a research assistant facilitated the testing sessions, documented feedback and monitored the interactions with the website. Afterwards, the videos were reviewed for content. Furthermore, participants filled out the System Usability Scale (SUS) [50, 51] and a written survey including purpose-designed open-ended (e.g. *“What do you like about the website?”*) and close-ended questions (e.g. *“Do you like the design of the website?”*). The SUS is a scale consisting of 10 items which gives a global subjective perception of the website usability. The mean total score of the SUS given by the three participants was 72.5 (range 0–100). A higher score indicates a better subjective usability perception. The website was adjusted and optimized to user-friendliness based upon feedback obtained in usability testing.

Finally, prior to commencing the RCT, the treatment manual, intervention and procedures were tested in a pilot study. It was intended that each participating therapist treats one highly-distressed CRCS so that four patients needed to be included. In total six patients were included by the screening procedure. One included patient dropped out before starting the intervention because of metastatic cancer. Another patient dropped out because of technical problems with the questionnaires and participation got too stressful. Therefore four patients started the treatment as intended. However, during the intervention two patients who scored above cut-off on the Distress Thermometer (≥5) during screening procedure appeared to have no perceived need for help. One of them dropped out of the study after three appointments with the therapist and the other stayed in the study until finishing the T1 questionnaire. Due to dropouts only three patients completed the CORRECT intervention. As a result of the pilot study, a check for self-perceived need for help with distress was added to the screening procedure. Further, a few minor changes were made in the homework exercises on the interactive website. After the pilot study, content of the CORRECT intervention and methodology were finalized.

#### Content of the intervention

The CORRECT intervention is designed to facilitate adjustment and coping and to reduce distress through changes in cognitions and behaviors. The blended therapy is tailored by the therapist in consultation with the patient to needs identified by the results of the baseline questionnaire. An online system (RadQuest software) processes the data of the baseline questionnaires and produces visual graphics into a report called the “Patient Profile Chart”, which helps interpret the results and identify problem areas [52]. Three different types of distress are targeted in the CORRECT-intervention: 1) distress due to physical consequences (gastrointestinal problems, stoma related issues, post-cancer fatigue, neuropathy, pain and sexual dysfunction), 2) anxiety and FCR, 3) depressive mood. These different types of distress are addressed in separate modules. The CORRECT-intervention is delivered over 14 weeks and consists of five individual F2F sessions of 1 h and three telephone consultations of 20 min, with simultaneous use of the self-management interactive website. The CORRECT-intervention starts with three weekly F2F sessions to discuss the Patient Profile Chart, develop the therapist-patient relationship, explain the therapy rationale, and select treatment module(s). Therapist support is gradually decreased towards the end of the intervention period, and self-management is increased through the greater use of the interactive website. This way, patients take charge of their own health and learn to cope more independently with future challenges. A similar treatment design has proven to be successful for managing FCR in breast, prostate and colorectal cancer survivors [53].

All sessions start with discussing the homework assignments which are completed on the website. In the first session the patient’s experiences of the cancer follow-up phase, current distress, unmet needs and treatment goals are discussed. The key problems and the goals of treatment are then determined. For each patient, at least one or a maximum of two modules are selected based on the initial assessment and the Patient Profile Chart. The order of the presentation is tailored to needs, with the most concerning problem addressed first. Each module has sufficient content to fill the duration of the intervention in the event that only one domain of need is identified. Patients have however free access to all the modules on the website. In the second session the therapist introduces and explains basic skills of CBT applied to the first module. The following sessions (session 3 to 7) include: psycho-education, cognitive restructuring, behavior modification and relaxation. During session 6 and 7 the therapist and patient evaluate distress reduction and discuss long-term consolidation of skills. During the final session (session 8) goal evaluation, on-going self-management, and relapse prevention are discussed. Detailed structure of the intervention can be found in Table 1.

**Table 1 Tab1:** Detailed structure and timeframe of the CORRECT-intervention

Week	General introduction module		Module 1		Module 2 (optional)	General closing module	
	Session	Web-based homework	Session	Web-based homework	Web-based homework	Session	Web-based homework
0		“Preperation to first session”					
1	1: F2F	“After the first session”					
2	2: F2F			Online 1			
3			3: F2F	Online 2			
4			4: Telephone				
5				Online 3			
6			5: F2F	Online 4			
7					Online 1		
8			6: Telephone				
9				Online 5	Online 2		
10					Online 3		
11			7: Telephone				
12					Online 4		
13					Online 5		“Preperation to last session”
14						8: F2F	“Closing: how to move on?”

#### Content of the interactive self-management website

The interactive self-management website is available to support the CRCS throughout the CORRECT intervention. After each F2F and telephone session, patients receive homework assignments via the website. CRCS who indicate they lack sufficient computer skills to use the website are provided with a paper workbook with identical content and a DVD or USB containing audio-visual materials. The website contains a general introduction module, the three specific modules and a general closing module (Fig. 2). The general introduction module consists of two online homework sessions including 13 exercises. These exercises focused on introducing CBT and identifying personal goals. After the general introduction module, each participant completes the chosen module(s) on the website. The three specific modules include different types of self-management activities. Each of the three specific modules has five online homework sessions with a range of 29–32 exercises, including psycho-educational scripts, assignments tasks, screening tests, audio clips, and peer videos. The peer videos were produced from edited filmed interviews between a clinical psychologist (JP) and four CRCS. Peer videos are included on the website for psycho-education and social comparison. The general closing module consists of two online homework sessions including nine exercises which are focused on goal evaluation and relapse-prevention.

**Fig. 2 Fig2:**
[figure not shown]
Homepage of the interactive self-management CORRECT website

#### Therapists

The therapists providing the intervention are four qualified, registered healthcare psychologists with > 10 years of experience in the field of medical psychology, psycho-oncology and/or experience in e-health therapies. All therapists completed a one-day training program and received 1 h training in use of the website. Before the trial started, three of the four therapists were able to complete treatment of one CRCS in the pilot study. All therapists used the therapist treatment manual under clinical supervision of two senior and experienced psychologists (JP, EC), of which one is a qualified CBT supervisor (JP). In both academic hospitals (Radboudumc and VUmc) two therapists are available. Therapists will be given biweekly group supervision with the two senior psychologists (JP, EC).

#### Treatment integrity

To ensure treatment integrity all therapists will use a standardized therapy manual, including therapist checklists for each session. All the F2F sessions will be audio taped. A random selection of 5% of audio-recordings will be reviewed to check fidelity to the treatment protocol.

### Control condition: care as usual

According to Dutch CRC clinical practice guidelines, survivors complete routine follow-up examinations for 5 years after completion of treatment [54]. The medical follow-up appointments are every 3–6 months during the first 2 years of follow-up, followed by (bi)-annual examinations for up to 5-years. Participants in the control condition will have access to usual care and routine follow-up. Dutch clinical practice guidelines currently stipulate that routine psychosocial screening using the Distress Thermometer should be carried out for all CRCS as part of standard follow-up care [55]. If distress is detected at screening during follow-up, CAU can be very diverse. For example, physicians or nurses may advise patients how to reduce distress or they may refer patients to their general practitioner, a social worker or a psychologist. No restrictions will be made to the CAU condition.

### Assessment

Demographic and medical information are obtained using self-report questionnaires and medical records. At three points in time (T0; baseline prior to randomization, T1; 4 months after baseline and T2; 7 months after baseline), participants are asked to complete online questionnaires using RadQuest software. Participants who do not wish to use the internet may opt for mailed paper-and-pencil questionnaires. Those who do not complete the questionnaires within 2 weeks receive a reminder from the researcher via email or by phone.

#### Screening instrument

Before inclusion in this trial, eligible patients complete a distress screening using the Distress Thermometer (DT). Patients rate their overall level of distress during the past week from 0 (no distress) to 10 (extreme distress) on a visual analog scale (the Thermometer). The DT has moderate to good internal consistency (α ranging from .60 to .90) [56, 57]. A cutoff point of ≥5 is used to identify high distress due to its optimal sensitivity, specificity and diagnostic accuracy [56, 58]. For screening in the current study, the thermometer score on the DT is used to determine eligibility. The Problem List of the DT contains 47 problems in practical, social, psychological, spiritual and physical domains; patients indicate the distress severity of each item on a 10-point scale. The Dutch version of the DT has an additional question about the wish for referral: “Would you like to talk with a professional about your problems?” [56].

#### Primary outcome

*Psychological distress* is assessed with the Brief Symptom Inventory 18-items (BSI-18) [59, 60]. The items of the BSI-18 are grouped into three subscales; anxiety, depression, and somatization. The BSI-18 gives a global severity index (GSI). The GSI is viewed as a reliable reference score sensitive to change and therefore is used to evaluate effects of psychotherapy [61]. The BSI is a valid instrument with high reliability in mixed cancer samples (α = 0.89) [59].

#### Secondary outcomes

*The perceived impact of physical consequences of colorectal cancer* is assessed with the valid and reliable Dutch version of the European Organization for Research and Treatment (EORTC) of Cancer Quality of Life Questionnaire Core 30 (QLQ-C30) [62, 63] and the 38-item colorectal cancer specific module (CR38) [64]. These questionnaires have shown good psychometric properties in survivors of cancer (α = 0.89) [62–64].

*Fatigue* is assessed using the Checklist Individual Strength (CIS) [65, 66]. The CIS is a 20-item questionnaire, designed to measure four aspects of fatigue; fatigue severity, concentration, motivation and physical activity. The CIS is a well-validated instrument [67, 68].

*Anxiety and depressed mood* is measured with the Hospital Anxiety and Depression Scale (HADS) [69, 70]. The HADS has demonstrated reliability and validity in oncology patients [71–73].

*Fear of cancer recurrence* is assessed with the Cancer Worry Scale (CWS). The CWS is able to detect dysfunctional levels of FCR [74, 75]. This scale is found to be a valid and reliable instrument in Dutch cancer survivors (α = 0.87) [75].

*Cancer-specific distress* will be assessed with a Dutch version of the Impact of Event Scale (IES). This scale measures cancer-related avoidant behaviors and intrusive cognitions [76–78]. The IES has shown good reliability (α ranging from .87 to .96) and construct validity [78].

*Self-efficacy* in dealing with distress following colorectal cancer will be assessed with the Self-Efficacy Scale (SES). This scale is previously used in measuring self-efficacy in patients with post-cancer fatigue [79, 80] and in breast cancer survivors [47].

#### Other outcome measures

*Health care utilization costs* are evaluated with a modified version of the Trimbos/iMTA questionnaire for Costs associated with Psychiatric Illness (TiC-P) [81]. Medical costs are assessed to identify health care usage (e.g. medication use/dose, visits to general practitioner or to other health care professionals). To further monitor cost-utility, the EuroQol-5D (EQ-5D) is used. The EQ-5D is a non-disease-specific instrument used to describe and value health [82, 83].

*Technical usage statistics* are obtained to evaluate website use and adherence. This is an important step in explaining how e-health interventions can cause behavior change and symptom improvement [84]. Data examined include frequency and duration of logins, type and number of opened online activities, frequency and duration of opened online activities, evaluation of online activities and number of submitted homework assignments to the therapists.

### Statistical analyses

Statistical analyses are being performed using SPSS. Key variables should be evenly distributed between conditions by randomization. To control for that, baseline characteristics are compared between participants in the intervention and CAU conditions with Chi-square (categorical variables) and ANOVA (continuous variables). Variables that are not evenly distributed are used as covariates in the analyses, along with time since end of treatment to control for the possible relationship between time since end of treatment and the level of distress. Analyses are on an intention-to-treat basis. A per-protocol analysis is amongst participants who successfully completed the intervention. ANCOVA-analysis of the change scores in the outcome variables is conducted to calculate differences between the two conditions. Exploratory sub-group analyses are conducted based on ‘time since end of treatment’, ‘age’, and ‘gender’. Caseness of the GSI is used to determine clinical significant improvement. Caseness is indicated if a T-score on the GSI scale > 62, or a T-score > 62 on two of the three clinical subscales. To analyze the difference between the proportions of patients meeting the criteria for clinically significant improvement at T1, chi-square tests are used.

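### Intention-to-treat is stated, but the named change-score ANCOVA cannot by itself include patients without a follow-up score; a repeated-measures model using T1 and T2 would be a cheap improvement

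*Protocol article*

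**What the plan says.** Three statements in the protocol article bear on this point.

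- Statistical analyses gives the principle: "Analyses are on an intention-to-treat basis". A separate analysis is restricted to those who finished the therapy: "A per-protocol analysis is amongst participants who successfully completed the intervention".
- The same section names the method for comparing the arms: "ANCOVA-analysis of the change scores in the outcome variables is conducted to calculate differences between the two conditions". The only visit it names is T1, for the chi-square test of clinically significant improvement.
- Sample size anticipates loss: "Taking into account a dropout rate of approximately 20% a sample of 160 patients (80 patients per condition) will be included at baseline".

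The Study design section places follow-up at 4 months (T1) and 7 months (T2), with the intervention delivered between baseline (T0) and T1. The article does not say how a patient without a T1 or T2 score is handled. It mentions neither imputation, nor a mixed model, nor exclusion.

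**The concern.** A change score is a follow-up value minus a baseline value, so it does not exist for a patient who did not return the questionnaire. Fitted to observed data, the named model uses only patients seen at the visit in question. It also makes no use of a patient's T1 score when T2 is missing.

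The setting makes this matter. The trial is unblinded, one arm has eight therapist contacts plus web homework over 14 weeks, and the other has usual care. The pilot withdrawals described under Developmental process were for metastatic disease, for questionnaire problems and stress, and for lack of perceived need for help. Such reasons can be related to distress and can differ by arm. At stake is a T2 treatment effect that is called intention-to-treat but rests on those who stayed.

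**Working it through.** **1. The plan's own figures.** The inputs are 128 analysable patients and 20% dropout (Sample size). 128 / (1 − 0.20) = 160, which reproduces the recruited number. Conversely, 160 × 0.20 = 32 patients are allowed for as lost, or 16 per arm if balanced. (A separate matter: the intermediate 190 does not lead to 128, since 190 × (1 − 0.6²) = 121.6, whereas 200 × 0.64 = 128. It does not affect this point.)

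**2. Power with and without those 32.** With d = 0.4 and r = 0.6, the residual SD is √(1 − 0.36) = 0.8, so the adjusted effect is 0.4 / 0.8 = 0.5. The noncentrality is 0.5 × √(N/4).

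- N = 128: 0.5 × √32 = 2.83, giving power of 80.7% (normal) or 80.1% (noncentral t), two-sided.
- N = 160: 0.5 × √40 = 3.16, giving power of 88.5% or 88.2%. This is an upper bound, reached only if all 160 gave complete data.

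A method that recovers part of the information lies between these values, so N does not need to change.

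**3. Simple bound on bias.** If fractions p₁ (intervention) and p₀ (usual care) drop out, and their outcomes are worse than those of completers in the same arm by δ₁ and δ₀ SD, a completer analysis overstates the benefit by p₁δ₁ − p₀δ₀. With p₁ = p₀ = 0.20, δ₀ = 0 and δ₁ = 0.2 to 0.5 (assumed), the overstatement is 0.20 × 0.2 = 0.04 to 0.20 × 0.5 = 0.10 SD. With δ₁ = δ₀ it is zero.

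**4. Simulation at T2.** From the plan: 80 per arm and true d = 0.40. Assumed: correlations T0–T1 0.6, T1–T2 0.7 and T0–T2 0.5; everyone seen at T1; T2 dropout logistic in T1 distress, with log-odds of 0.5, 1.0 or 1.5 per SD; 4,000 replicates. The observed-case analysis is baseline-adjusted ANCOVA of T2 change. The comparator is the likelihood-based estimate that also uses T1.

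| T2 dropout, intervention / usual care | Driven by T1 distress in | Observed-case ANCOVA | Using T1 |
|---|---|---|---|
| 28% / 15% | intervention arm only | 0.45, 0.50, 0.53 | 0.40 |
| 28% / 15% | both arms | 0.42, 0.44, 0.46 | 0.40 |
| 20% / 20% | intervention arm only | 0.44, 0.47, 0.49 | 0.40 |
| 20% / 20% | both arms | 0.40 throughout | 0.40 |
| 28% / 15% | neither (random) | 0.40 | 0.40 |

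The three values in a cell correspond to the three log-odds. Bias arises when the link between T1 distress and dropout differs by arm, and unequal rates are not required. The estimate using T1 also had a slightly smaller standard error. A very steep dependence in one arm (log-odds 4 per SD) takes observed-case ANCOVA to just under 0.6. If patients with low distress were the ones to leave the intervention arm, the bias would run the other way.

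**5. T1.** A patient who never returns after baseline has no intermediate score to draw on. For the T1 contrast, a mixed model adjusted for baseline then gives essentially the same answer as observed-case ANCOVA.

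**The case against.** The strongest reply is that the article does not commit to a completer analysis. Intention-to-treat, then imputation, then ANCOVA of change scores is consistent with every sentence in Statistical analyses. An article commonly leaves missing-data handling to the full protocol or analysis plan, which is not at hand. Read next to the per-protocol sentence, intention-to-treat may simply mean analysis as randomised whether or not therapy was completed, and stopping therapy does not itself remove a change score. Inflating the sample for dropout is ordinary practice and does not contradict intention-to-treat. The Assessment section also provides reminders and a paper option, which should limit loss.

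All of this stands, and it rules out three readings a reader might be tempted to draw: that the plan specifies exclusion of everyone without follow-up, that 32 patients are already written off from the analysis, and that T1 and T2 are to be analysed separately. The text states none of these.

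Two further objections also hold. The size of any bias depends on the dropout pattern chosen, and none of those patterns comes from the documents. A mixed model also leaves out patients with no follow-up at all, so it does not make the analysis complete.

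What remains is narrower. The article does name its method for comparing the arms, and a model that uses both follow-up visits is at least as good in every scenario tried and needs no new data.

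**Conclusion.** The point holds as a cheap improvement, not as a contradiction that must be repaired before the trial can be interpreted. The stated principle covers all randomised patients. The named model cannot do so on observed data, and about 32 of 160 are allowed for as dropouts.

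For T2, observed-case ANCOVA gave 0.40 to 0.53 for a true 0.40 under the main scenarios, an overstatement of 0 to 0.13 SD. That range rests wholly on the assumed correlations, dropout rates and dependence on T1. It shrinks to nothing when dropout is equal and similarly driven in both arms, and its sign could reverse. A reader might infer that the trial's headline result will be inflated by a particular percentage. The documents do not support that: no dropout pattern is given, and the gain shown is at T2. T1, the visit at the end of the intervention, gains little.

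**What to change.** For the BSI-18, replace the change-score ANCOVA with one likelihood-based linear mixed model.

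- Responses: T1 and T2 as repeated measures, including every randomised patient with at least one follow-up score.
- Terms: arm, time, arm-by-time, baseline score and the stratification factors (academic hospital, gender, colon or rectal diagnosis).
- Result: the arm contrast read off at each visit.

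ANCOVA after multiple imputation that uses T1 is an equivalent route if the team prefers to keep ANCOVA. In either case, add a delta-adjusted multiple-imputation sensitivity analysis that covers all 160 randomised, including those with no follow-up, and state in the text how such patients enter the intention-to-treat analysis.

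The plan already states "Statistical analyses are being performed using SPSS", and its MIXED procedure fits this model. The cost is a few sentences and modest extra programming. The downside is that the main model assumes data are missing at random, which the sensitivity analysis is there to test. No new data are needed and N stays at 160. The choice should be fixed before outcome data are seen, so that it cannot be guided by the result.

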### Participant eligibility

CRCS are eligible to participate in this study if they: 1) are 18 years or older; 2) are cancer free at study entry; 3) have completed primary CRC treatment with curative intent (stage I, II or III) between 6 months and 5 years previously; 4) have high distress levels indicated by a score of ≥5 on the Distress Thermometer; 5) have basic Internet skills (e.g. possession of an email address, Internet access at home); 6) are literate in Dutch; and 7) are able to travel to the academic hospital for F2F sessions. Ineligibility criteria include: 1) diagnosis of Lynch Syndrome; 2) active psychotherapeutic treatment at study entry; and 3) inability to provide informed consent due to intellectual disability or cognitive impairment.

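### Clinically significant improvement is tied to BSI-18 caseness at T1 with no baseline-case requirement and no denominator, although patients enter on the Distress Thermometer

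*Protocol article*

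**What the plan says.** All references are to the protocol article.

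- **Statistical analyses, criterion.** "Caseness of the GSI is used to determine clinical significant improvement". The cut-off follows: "Caseness is indicated if a T-score on the GSI scale > 62, or a T-score > 62 on two of the three clinical subscales".
- **Statistical analyses, test.** "To analyze the difference between the proportions of patients meeting the criteria for clinically significant improvement at T1, chi-square tests are used".
- **Statistical analyses, analysis set.** "Analyses are on an intention-to-treat basis".
- **Participant eligibility.** Patients must "have high distress levels indicated by a score of ≥5 on the Distress Thermometer". No BSI-18 threshold is among the criteria.
- **Screening instrument.** It confirms that "the thermometer score on the DT is used to determine eligibility".
- **Primary outcome and Assessment.** The BSI-18 is the primary outcome instrument. Questionnaires are completed at T0, T1 and T2, so baseline caseness can be derived for every patient.

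The text does not say whether an improved patient must have been a case at T0, how much change is needed, or which patients form the denominator.

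**The concern.** Improvement is a change, but the only criterion given describes a state. That would do little harm if every patient entered as a BSI-18 case. Here entry rests on a different instrument: one 0 to 10 rating of distress over the past week, given at screening. The BSI-18 is completed later, after a telephone contact and written consent. A patient can therefore qualify on the thermometer and still be below the BSI-18 cut-off at T0.

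The pilot study gives a mild indication that the thermometer is a loose marker. Two patients above its cut-off turned out to have no perceived need for help. This is not a BSI-18 result, and the need-for-help check added afterwards does not impose BSI-18 caseness either.

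At stake is the meaning of the reported percentage improved, and the size of the contrast between arms, in the one analysis in that section that addresses clinical significance.

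**Working it through.** **Figures in the article.** There is none for the caseness comparison: no baseline caseness rate, no remission rate and no power statement. The Sample size section gives 160 patients and about 20% dropout, so 160 × 0.8 = 128 evaluable, or 64 per arm.

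**Notation.** Let c be the share of patients who are cases at T0, r_I and r_C the proportions of those cases who are non-cases at T1 (intervention, control), and s the proportion of baseline non-cases still non-cases at T1, taken as equal in both arms.

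**Three readings that the wording allows**

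- A: improved = non-case at T1, all patients. Proportion = c·r + (1 − c)·s.
- B: improved = case at T0 and non-case at T1, all patients in the denominator. Proportion = c·r.
- C: improved = case at T0 and non-case at T1, baseline cases only. Proportion = r.

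The difference between arms is c·(r_I − r_C) under A and under B, and r_I − r_C under C. The term in s cancels under A, so the dilution does not depend on s as long as s is the same in both arms.

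**First illustration.** Assumed: r_I = 0.50, r_C = 0.25, s = 0.90. Proportions are intervention vs control.

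| c | A | B | Difference, A or B | C |
|---|---|---|---|---|
| 0.3 | 0.15 + 0.63 = 0.78 vs 0.075 + 0.63 = 0.705 | 0.15 vs 0.075 | 7.5 points | 0.50 vs 0.25 |
| 0.4 | 0.20 + 0.54 = 0.74 vs 0.10 + 0.54 = 0.64 | 0.20 vs 0.10 | 10 points | 0.50 vs 0.25 |
| 0.6 | 0.30 + 0.36 = 0.66 vs 0.15 + 0.36 = 0.51 | 0.30 vs 0.15 | 15 points | 0.50 vs 0.25 |

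Against C, reading A inflates the proportion in both arms and reading B deflates it. Under A with c = 0.4, 0.54 / 0.74 = 73% of the intervention patients called improved were not cases at T0. That figure has no counterpart under B or C.

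**Second illustration, with power.** Assumed: r_I = 0.50, r_C = 0.30, s = 0.95, 64 evaluable per arm, two-sided 5% test of two proportions.

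| c | Difference, A or B | Power A | Power B | Power C (difference 20 points) |
|---|---|---|---|---|
| 1.0 | 20 points | 0.64 | 0.64 | 0.64 |
| 0.8 | 16 points | 0.44 | 0.49 | 0.54 |
| 0.6 | 12 points | 0.29 | 0.35 | 0.43 |
| 0.4 | 8 points | 0.17 | 0.23 | 0.31 |

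Under A with c = 0.6, (1 − 0.6) × 0.95 = 0.38, so 38 of every 100 patients would be labelled improved without having been cases at T0. Moving s between 0.90 and 1.00 changes power under A at c = 0.4 only from 0.16 to 0.18.

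**The case against.** The strongest reply is that the article never says a T1 non-case counts as improved whatever the baseline status. Improvement ordinarily implies moving out of a worse state. Reading C is compatible with the wording, and the T0 data to apply it are collected. A condensed article may leave the operational detail to the full protocol or the SAP. This stands in part: a reader might infer that the plan has adopted reading A, and the text does not establish that. But the article does fix a criterion, a cut-off, a time point and a test under intention to treat. As worded, these admit two all-patient readings in which the result does not mean what its name says.

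Other points stand in full:

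- Inflation, and the 73% figure, belong to reading A only. Reading B goes the other way.
- Every rate used above is assumed. That some patients are BSI-18 non-cases at T0 is possible under the entry criteria but not shown by the article.
- Caseness at T1 compared between all randomised patients is a valid intention-to-treat contrast, and chi-square is a valid test of it. A smaller difference in that population is a different quantity, not a wrong one. What misleads is calling it improvement.
- A reader might infer that the trial's clinical conclusion rests on this comparison. The documents do not support that. The primary outcome is BSI-18 distress analysed by ANCOVA, the sample size was set for that analysis, and caseness is not listed as an outcome in its own right.
- Restricting to baseline cases is costly. At c = 0.4 it leaves about 0.4 × 64 = 26 evaluable patients per arm.

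**Conclusion.** The point holds as a badly fixed definition. The section ties improvement to a single-time-point status on an instrument that does not govern entry, and states neither a baseline-case requirement nor a denominator. Under either all-patient reading, the difference between arms is the baseline case share times the difference among cases. With the assumed 50% vs 25% remission, 25 points becomes 7.5 points at 30% cases and 15 points at 60%. The true size cannot be fixed from the article. The scaling also assumes no treatment effect among baseline non-cases; under reading A, an effect that kept non-cases from becoming cases would add to the difference.

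The consequence is confined to this analysis: a misleading label and a weaker contrast. Randomisation protects the comparison from bias between arms, and the primary ANCOVA is untouched. The definition should be corrected, but it does not threaten the trial's main result.

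**What to change.** 1. Define clinically significant improvement as BSI-18 case at T0 and non-case at T1, with baseline cases as the denominator. Baseline status is fixed before randomisation, so the comparison within this subset remains a randomised one.
2. For all randomised patients, label the analysis *caseness at T1*, not improvement. Replace the raw chi-square with logistic regression adjusted for T0 caseness or T0 GSI and for the stratification factors (academic hospital, gender, diagnosis).
3. Report baseline caseness by arm. It is not a stratification factor, so the number of cases may differ between arms.

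**Cost.** This is a change of wording and analysis only; the T0 BSI-18 is already collected. The improvement analysis has fewer patients and lower precision. In the second illustration its power at 40% baseline cases is still only 0.31, against 0.17 or 0.23 under the all-patient readings, so it should be presented as an estimate with its confidence interval. The adjusted logistic model keeps all randomised patients.
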